#### Secondary outcome(s)

Difference in proportions of infants with developmental delay between the DHA and placebo group at 12 months. Developmental delay will be defined as a DASII score ≤ 70.Mean difference in infant size (weight, length and head circumference) and APGAR score at birth.Mean change in infant size (weight, length and head circumference) at birth, 1 month, 6 months and 12 months between the DHA and placebo group.Mean difference in number of still births, preterm and low birth weight babies between DHA and placebo groups.Difference in infant morbidity patterns (types of illness, frequency and duration of specific conditions) between DHA and placebo group.

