### Effect size, power and sample size

The primary outcome variables are infant motor and mental development quotient at 12 months of age. The smallest effect sizes of interest were 0.25 S.D. for motor and mental development at 12 months of age [42]. Using a two-tailed test and a significance level of α = 0.05, a final sample of 338 infants per group (676 mother-child dyads) was required at the end of the study (12 months postpartum) to provide 90% power. A total of 957 mothers have been recruited in the present study, allowing for potential attrition due to serious adverse events, withdrawal, and migration out of the study area. Breast-milk samples are being collected within 3–4 days after delivery and at 1 month and 6 months postpartum from a 30% convenience sub-sample - 150 mother-infant pairs per group, which will have 95% power to detect effect sizes of 0.5 S.D. in DHA levels.

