### Randomization procedure

Consenting women were randomized to their treatment group by the project officer. The randomization scheme consisted of a sequence of blocks such that each block contained a pre-specified number of treatment assignments in random order. The block size of 2, 4 and 6 was used for treatment allocation. The randomization code list was pre-generated for 1200 women randomly allocating 600 participants to the DHA and 600 participants to placebo group. The assignment codes were placed in sealed envelopes at the beginning of the study, and these envelopes were kept sealed at the host institution by a staff-member not involved in the trial.

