Secondary outcomes:Birth outcomes – Data are collected by a research assistant from hospital records within 24 h after delivery. In case of night deliveries, records from hospital staff are obtained the next morning. All hospital staff were apprised of the variables being collected, procedures and data collection methods before the start of the trial. A periodic (every 6 months) refresher training has also been provided to the staff. The data include whether the birth was a live birth, sex of baby, type of delivery, and anthropometric measurements. Birth weight is measured to the nearest 10 g by using a digital pediatric scale. Low birth weight is defined as recorded birth weight less than 2500 g. Birth length and head circumference are measured by trained hospital staff to the nearest 1 mm using a portable anthropometer with a fixed headpiece and a flexible tape, respectively, according to standard procedures. Gestational age at birth in days is determined based on the dating ultrasound. Preterm delivery is defined as delivery after 20 weeks and before 37 weeks of completed gestation. Foetal losses during pregnancy – including miscarriages/abortions and still-births are recorded by study personnel on site or details are brought by field workers (in case mother went to any other hospital). Stillbirths are defined as fetuses delivered at 20 weeks of gestation or later with no signs of life and recorded as occurring before or during the onset of labor; neonatal deaths are defined as deaths among live-born infants occurring within 28 days after delivery.Infant weight, length and head circumference at 6 and 12 months are measured during their scheduled PKH visits. Questions about infant’s health are asked by the field-staff during home-visits (postpartum). Copies of the health-reports from the child’s paediatrician (whether at PKH or elsewhere) are collected. After the screening procedure, at the time of recruitment, data for contact information, maternal obstetric medical history, demographic details and socio-economic status also have been collected by the trained research assistant using pre-tested questionnaires. Anthropometric measurements of both mother and father have been recorded. Dietary intakes of fatty acids were evaluated using a previously validated food-frequency questionnaire adapted for use in pregnant women (recall period- past 3 months) also have been recorded.Fatty acid profile: Fatty acid composition of RBC membrane phospholipids are appropriate biomarkers of fatty acid status and reflects dietary intakes. Linoleic acid (18:2n-6); Alpha-linolenic acid (18:3n-3); Arachidonic acid (20:4n-6); Eicosapentanoic Acid (20:5n-3); DHA (22:6n-3) will be measured for this study. Lipids will be extracted form the RBC membrane, phospholipid fraction will be separated by thin layer chromatography (TLC), esterified by procedure described by Lepage and Roy [49] and subjected to gas chromatography (GC) for separation and identification. Non fasting maternal blood samples (5 ml) were obtained by veni-puncture at recruitment, delivery and 6 months postpartum. Neonatal blood samples were obtained from the umbilical cord vein immediately after delivery using the syringe method [50]. A 2 ml venous blood sample was obtained 12 months of age from infants. All samples were collected into tubes containing disodium ethylene diamine tetraacetic acid (EDTA). Plasma and RBCs were separated by cold centrifugation at 800 g for 10 min. Plasma was aliquoted and stored at − 80 °C for later analysis.Breast-milk polyunsaturated fatty acids (PUFAs): Breast-milk samples (1 day, 1 month and 6 months postpartum) are taken from 30% random sub-sample. The milk-samples are from a morning feed but not the first one, between 8 and 12 o’clock at PKH. Infants are allowed to suckle the nipple for a few minutes, and then a breast-milk sample (10 ml) is expressed (manual, by mothers themselves) and the feeding continued [51]. The samples are refrigerated immediately (to prevent bacterial growth) and later aliquoted into smaller containers, filled nearly to the top to minimize oxidation, and frozen at − 80 °C until analysis. Before storage, butylated hydroxytoluene is added to a final concentration of 75 μg/mL to prevent lipid oxidation. Since breast-milk PUFA will be expressed as a percent of total fatty acids, complete breast expressions are not required. The samples will be analysed by gas chromatography using standard methods [52].

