### Statistical analyses

All the analyses will be performed on the principle of ‘intention to treat’ unless otherwise specified (i.e., we will compare patients in the groups to which they were originally randomly assigned). Statistical analyses will be performed using STATA Version 14.0. We will summarize maternal and household characteristics in the two groups and assess the effectiveness of randomization by comparing these between the groups. Continuous, normally distributed variables will be summarized as means and standard deviations, while skewed variables will be summarized as medians and inter-quartile ranges. Categorical/binary variables will be summarized using proportions. Comparisons on baseline characteristics will also be made between the final study sample and those who were lost to follow up.

For the primary outcome, we will test the unadjusted difference in the mean DASII score at 6 months and 12 months between the two treatment groups using a two-sample t-test. For adjusted analyses, we will consider the DASII score as a continuous variable and use a multiple linear regression model, adjusting for treatment, sex of the child, maternal age, maternal education, socio economic status, birth-weight and other factors which we find out to be significant at baseline comparison. We will adjust for the 6 month DASII score in the model examining the difference in score at 12 months between the treatment groups using Generalized Estimating Equation (GEE) analyses to account for correlation between the 6 month and 12 month DASII score.

The DASII score will also be analysed as a binary variable. DASII score ≤ 70 will be used to defined developmental delay. The unadjusted and adjusted relative risk in the proportion of DASII score (≤70) at 12 months between DHA and placebo groups will be calculated using a log-binomial regression. In case of convergence issues with the log-binomial model, logistic regressions will be used to conduct the adjusted analyses and adjusted odds ratios will be reported instead of adjusted relative risks.

The differences in weight, length, head circumference, still birth, Apgar score at 1 min & 5 min of the infants at birth will be tested using t-test. Adjusted analyses will be performed using multiple linear regression.

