For longitudinal analysis of weight, length and head circumference (i.e. at birth, 1 month, 6 month and 12 month), we will also compare the average growth trajectories of the infants between the treatment and placebo groups using Generalized Estimating Equation (GEE) models. The adjusted analyses will also be performed adjusting for time, maternal weight and height, breast-feeding practices and maternal dietary intake.

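### The adjusted infant-growth model names its covariates but omits infant sex, a modest and avoidable loss of precision in a secondary analysis

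*Protocol article*

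**What the plan says.** All places are in the protocol article.

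- **Outcome.** Under Secondary outcome(s), infant growth is defined as "Mean change in infant size (weight, length and head circumference) at birth, 1 month, 6 months and 12 months between the DHA and placebo group".
- **Growth model.** Under Statistical analyses, the growth paragraph begins "For longitudinal analysis of weight, length and head circumference (i.e. at birth, 1 month, 6 month and 12 month" and compares average trajectories between arms by GEE. On covariates it says: "The adjusted analyses will also be performed adjusting for time, maternal weight and height, breast-feeding practices and maternal dietary intake". No open-ended clause follows.
- **DASII model.** The same section specifies multiple linear regression "adjusting for treatment, sex of the child, maternal age, maternal education, socio economic status, birth-weight", and then leaves room for further factors that differ at baseline.
- **Availability of sex.** Under Data collection, for birth outcomes taken from hospital records: "The data include whether the birth was a live birth, sex of baby, type of delivery, and anthropometric measurements".
- **Birth-size models.** For size at birth the article says only "Adjusted analyses will be performed using multiple linear regression", with no covariates named.
- **Randomisation.** "The block size of 2, 4 and 6 was used for treatment allocation". No stratification is described, and none by infant sex would be expected at enrolment.

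**The concern.** The plan chose to write out the covariates of the growth model, and the list leaves out one that is valid, already collected and used elsewhere in the same section. An infant's sex is fixed at conception and women are enrolled during pregnancy, so supplementation cannot alter it. Adjusting for it is therefore safe even though it is recorded after randomisation. Its presence in the DASII model shows that the plan has no policy against it.

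If boys and girls differ in size, two things follow when sex is left out. The difference adds to the residual variance of each growth outcome. And if the arms happen to differ in their proportion of boys, that difference passes uncorrected into the DHA-placebo estimate. Infant anthropometry is a stated secondary objective, so precision here is worth having when it costs almost nothing.

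**Working it through.** **1. The plan's own figure.** The article states 338 infants per group for 0.25 SD, two-sided α = 0.05 and 90% power. The two-sample formula gives n = 2(1.960 + 1.282)²/0.25² ≈ 337 per group, and power at 338 is 90.1%. The figure reproduces. It was set for the DASII scores; the article gives no effect size or power for growth. It is used below only as a benchmark number of infants, in step 3.

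**2. Precision at a single visit.** The documents give no boy-girl gap, so this input is an assumption. Let d be the gap in within-sex SDs, with half the infants boys. Sex then adds d²/4 to a within-sex variance of 1, so

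R² = (d²/4) / (1 + d²/4), and SE with sex ÷ SE without sex = √(1 − R²).

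| Assumed d | R² | SE ratio | SE reduction |
|---|---|---|---|
| 0.2 | 0.01/1.01 = 1.0% | 0.995 | 0.5% |
| 0.4 | 0.04/1.04 = 3.8% | 0.981 | 1.9% |
| 0.6 | 0.09/1.09 = 8.3% | 0.958 | 4.2% |
| 0.8 | 0.16/1.16 = 13.8% | 0.929 | 7.1% |

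The SE ratio does not depend on the sample size. R² is also the share of the sample that adjustment is worth, about 1% to 14%.

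**3. Chance imbalance.** With 338 per arm, the SD of the difference in proportion of boys is √(0.25 × 2/338) = 0.0385, or 3.8 percentage points. The 95% limit is 1.96 × 0.0385 = 0.075. An imbalance of that size shifts an unadjusted difference by 0.075 × d, which is 0.015 within-sex SD at d = 0.2 and 0.060 at d = 0.8.

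**4. Change over time.** The secondary outcome is worded as change, so step 2 does not carry over directly. Let the gap be G₀ at birth and G₁₂ at 12 months, in the units of measurement. The sex contribution to within-infant change is G₁₂ − G₀. With σ_c the within-sex SD of change, the formula in step 2 applies with d_c = (G₁₂ − G₀)/σ_c. If the gap is constant, d_c = 0, R² = 0 and nothing is gained. If it varies with age, a sex main effect alone will not absorb it, because that term is the same at every visit; a sex-by-time term is needed. The documents do not allow d_c to be estimated.

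**The case against.** The strongest reply is that this is a condensed article, that full covariate lists are usually left to the analysis plan, and that the growth list does not claim to be exhaustive: it omits even treatment, which the model must contain. The word for *in addition* in that sentence might also be read as extending the DASII covariates. This does not remove the point. Treatment is implied by the comparison itself. The sentence is more naturally read as adding adjusted analyses to the unadjusted comparison. And the article did not leave the list to another document. If the sponsor did mean the DASII covariates to carry over, the same one-line edit would make that clear.

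It can also be said that sex-standardised scores may be intended, which would dispose of the matter. The article names only the measurements and mentions no standardisation, so this cannot be assumed.

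Several parts of the objection stand:

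- The boy-girl gap is assumed, and the single-visit calculation contains no other covariates, whereas the planned model includes maternal weight and height.
- A time-constant gap cancels from within-infant change.
- A reader might turn the SE reduction into a power gain. At 338 per group and 0.25 SD, power would move from 90.1% to between 90.4% and 93.8% over the range above. The documents do not support this as a statement about growth, because both the effect size and the sample size belong to DASII.
- A reader might infer that the growth comparison is biased or not credible. Randomisation balances sex in expectation, and the unadjusted SE already allows for chance imbalance. Sex-differential loss to follow-up is possible, but nothing in the article shows it, and comparisons of retained with lost participants and multiple imputation are planned.
- The article names no covariates for the birth-size regressions. That is silence, not an error.

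**Conclusion.** The point holds as a small, worthwhile improvement. The listed covariates of the adjusted growth model leave out a valid prognostic candidate that is already collected and already used for DASII. The consequence is a modest loss of precision, with no correction for chance sex imbalance, in a secondary analysis. Type I error is not inflated, no design figure is contradicted, and the primary outcome is unaffected.

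The size rests on an assumed gap of 0.2 to 0.8 within-sex SD and an even sex split: about 0.5% to 7% off the SE at a single visit. For change over time the gain depends on how far the gap varies with age, which the documents do not give, and it could be nil.

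**What to change.** In the growth paragraph of Statistical analyses, add infant sex and a sex-by-time term to the covariates of the adjusted GEE for weight, length and head circumference. Specify this before the analysis team is unblinded, which the Blinding section places after the last infant turns one, so that it cannot look like a choice made after seeing the results.

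Preferably, name the same sex term in the adjusted regressions for weight, length and head circumference at birth, where the article currently lists nothing.

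Sex-standardised scores are not a like-for-like substitute: they change the outcome scale and need a chosen reference standard.

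The cost is one main effect and, with four visits treated as categories, three interaction parameters per outcome. That is negligible against about 676 infants. No new data are needed.

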### Subgroup analyses

The following apriori subgroup analyses will be carried out to evaluate potential heterogeneity of effect:Maternal Age (18–20; 21–25;26–30;31–35 years)BMI categories(< 23;≥ 23 Kg/m^2^)ParityGravidae (primi versus multi)Dietary patterns (Vegetarian versus non-vegetarian diet)Physical activity (Moderate versus sedentary)Gestational age (< 32; 30–32; 32–35;35–38; ≥38 weeks)Compliance (< 80%, 80–90%,> 90%)Duration of supplementation

The results of these subgroup analyses will be treated with caution as this study is not powered for this analyses. In each subgroup analyses, a model will include the subgroup variable along with its interaction with treatment. A test of whether the treatment affects across the levels of the subgroup will be constructed by assessing the significance of the interaction.

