### DHA and neurodevelopment

Long chain polyunsaturated fatty acids, particularly DHA (22:6n-3) and arachidonic acid (20:4n-6), are integral to fetal, neural and retinal development and accrete extensively in the last trimester of pregnancy [25]. Despite the implications for child development, there have been few studies which have comprehensively tested interventions in humans. Makrides et al. showed that high-DHA (approximately 1% total fatty acids) enteral feeds compared with standard DHA (approximately 0.3% total fatty acids) from day 2 to 4 of postnatal life showed significantly higher (unadjusted mean difference, 4.7; 95% CI, 0.5–8.8; adjusted mean difference, 4.5; 95% CI, 0.5–8.5) Bayley’s Mental Development Index scores in Australian girls, however among the boys, it did not differ between groups [26, 27]. Ramakrishnan et al. [28] summarized studies in this area and reported that observational studies indicated a direct association between poor n–3 fatty acid status and increased risk of maternal depression and childhood behavioral disorders such as attention-deficit hyperactivity disorder (ADHD). It has also been hypothesized that prenatal exposure to DHA may also affect later development through fetal programming of the central nervous system and various other physiologic pathways. Ramakrishnan et al. in 2016 reported a beneficial impact of prenatal DHA supplementation on attention in preschoolers at 5 years of age where DHA group children recorded significantly fewer omissions (< 40) as compared to the control group on K-CPT (Conners’ Kiddie Continuous Performance Test). Also, the magnitude of positive association between home stimulation and cognitive functioning was found to be less in the DHA group (b = 0.71; 95% CI: 0.13, 1.29; placebo group: b = 1.71; 95% CI: 1.09), [29]. Another randomized trial, the DHA Intake and Measurement of Neural Development (DIAMOND) study [16] suggested some benefit of DHA supplementation of infants form 1–9 days of age till 12 months on visual acuity of infants at 1 year of age. It was observed that infants fed with control formula had significantly poorer visual acuity than the infants who were fed with DHA-supplemented formulas (*P* < 0.001). Evidence for association between increased consumption of sea food in pregnancy and improved neurodevelopmental outcomes in their children have also been shown in observational studies [30–33]. However, evidence from intervention trials from low- and middle-income settings is scanty. Most of the studies reviewed were conducted in developed countries. Some trials had small sample sizes too. Thus large, well-designed, community-based prevention trials from developing countries are warranted.

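### Subgroup list mixes baseline variables with gestational age at delivery and compliance, which arise after randomisation, and the printed gestational-age bands overlap

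*Protocol article*

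**What the plan says.** The Subgroup analyses section of the protocol article introduces its list by stating that "apriori subgroup analyses will be carried out to evaluate potential heterogeneity of effect". Alongside maternal age, BMI, parity, gravidity, diet and physical activity, it names "Gestational age (< 32; 30–32; 32–35;35–38; ≥38 weeks" and "Compliance (< 80%, 80–90%,> 90%)Duration of supplementation". Every variable is handled alike: "a model will include the subgroup variable along with its interaction with treatment", and the significance of the interaction is the test. The only caution offered is that the trial is not powered for these analyses.

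Other sections show when these variables become known:
- **Entry.** Study population and Table 2 put every woman at 20 weeks of gestation or less.
- **Gestational age.** The abstract and Study design name it as a secondary outcome. Data collection measures it at birth.
- **Compliance.** Monitoring adherence defines it as capsules consumed as a percentage of capsules expected, from counts at home visits.
- **Duration.** "Duration of supplementation" has neither a definition nor cut-points.

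**The concern.** A treatment-by-subgroup interaction compares the treatment effect across levels of a variable. If the variable is fixed before randomisation, the arms are comparable within each level. If it is settled afterwards, treatment or side effects may decide who lands in which level, and the women compared within a level need not be alike.

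The likeliest harm is a compliance gradient. If the DHA arm looks better among women who took more than 90% of capsules and no better among those below 80%, it will be read as dose-response. The same pattern arises if women who tolerate or persist with the active capsules differ prognostically from those who persist with placebo. The stated low-power caution does not cover this, because it is bias and not imprecision. The Discussion looks ahead to national nutrition programmes, where such a gradient, labelled a priori, could carry weight.

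Separately, a factor whose levels overlap cannot enter a regression as the section describes.

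**Working it through.** **1. When each variable is known**

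| Variable | Known at | Baseline? |
|---|---|---|
| Gestational age, <32 to ≥38 weeks | Delivery: with entry at ≤20 weeks, bands of gestational age at entry would put every woman in <32 | No; a secondary outcome |
| Compliance | Capsule counts after allocation | No |
| Duration of supplementation | Not defined. Planned prenatal duration follows from gestational age at entry; realised duration depends on length of gestation and on stopping | Only if planned duration is meant |
| Age, BMI, parity, gravidity, diet, activity | Can be taken at enrolment | Yes |

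**2. Are the gestational-age bands a partition?** Placing values in the bands as printed, end-points included:
- 30 to just under 32 weeks: in <32 and in 30–32.
- 32 weeks: in 30–32 and in 32–35.
- 35 weeks: in 32–35 and in 35–38.
- 38 weeks: in 35–38 and in ≥38.

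They are not mutually exclusive. Reading <32 as a misprint for <30 removes the first overlap but not the shared edges at 32, 35 and 38.

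**3. Size for compliance**

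*From the plan:* 676 infants (338 per group), effect of interest 0.25 SD, two-sided α = 0.05. As a check on the plan's own figure, 0.25 SD at 90% power needs 337 per group, which agrees with 338.

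*Assumed:* a true effect of 0.25 SD for everyone, so no effect modification exists. An unmeasured factor U has correlation 0.5 with DASII. It has correlation r with a normal compliance score in the DHA arm and none in the placebo arm. The score is cut at −0.8 and 0 SD into low, middle and high.

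*Closed form:* apparent effect in a band = 0.25 + 0.5 × r × E[Z | band], with Z standard normal.
- Low: E[Z] = −φ(0.8)/Φ(−0.8) = −0.290/0.212 = −1.37
- Middle: E[Z] = (0.290 − 0.399)/0.288 = −0.38
- High: E[Z] = 0.399/0.5 = 0.80

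At r = 0.3: low 0.25 − 0.15 × 1.37 = 0.04; middle 0.25 − 0.15 × 0.38 = 0.19; high 0.25 + 0.15 × 0.80 = 0.37.

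*Simulation:* 2000 trials of 676 per setting, with the interaction F-test on 2 and 670 degrees of freedom.

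| r in DHA arm | Low | Middle | High | Interaction declared at 5% |
|---|---|---|---|---|
| 0 | 0.24 | 0.25 | 0.25 | 4.9% |
| 0.2 | 0.11 | 0.21 | 0.33 | 15.8% |
| 0.3 | 0.04 | 0.20 | 0.37 | 32.5% |
| 0.5 | −0.09 | 0.16 | 0.45 | 71.5% |

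**4. Size for gestational age at delivery**

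*Assumed:* mean 39 weeks, SD 1.8; U has correlation 0.5 with both gestation and DASII; true effect 0.25 SD throughout; illustrative cuts at 38 and 40 weeks; DHA lengthens gestation by d days.

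| d (days) | Effects within the three bands (SD) | Interaction declared at 5% |
|---|---|---|
| 0 | 0.24, 0.25, 0.25 | 5.5% |
| 2 | 0.22, 0.21, 0.22 | 5.4% |
| 4 | 0.19, 0.18, 0.19 | 5.8% |
| 7 | 0.14, 0.13, 0.16 | 5.5% |

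The Monte Carlo standard error at 5% is √(0.05 × 0.95/2000) = 0.5 percentage points, so the test is at its nominal level. The within-band effects are too small by roughly 0.03 SD at 2 days, 0.06 at 4 and 0.11 at 7, by a similar amount in each band. That common shift is why the interaction test does not register it.

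**The case against.** The strongest reply is that these are secondary explorations that the authors already promise to treat with caution, and that the randomised primary analysis is untouched. Both parts are true, and they limit the severity. They do not remove the point, because the caution concerns power, and low power neither describes nor excuses a comparison that is no longer randomised.

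Other replies have force:
- **At delivery is an inference.** The section says only gestational age. But no other reading of those bands separates anyone.
- **Duration could be planned duration.** This stands. The article does not define it, and a full protocol or analysis plan may. It should not be counted as post-randomisation outright.
- **The bands may be a slip.** Probably so for <32, and shared edges are common shorthand. The text as it stands still is not a usable factor.
- **The numbers are assumed.** They are. The documents give no data on how compliance relates to prognosis in either arm, and with r = 0 the compliance test holds its level.

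A reader might infer more than this, and three such readings are not supported. One is that an interaction on these variables could never reflect true effect modification. It could; the trial could not tell it apart from selection. Another is that the multiplicity of the list (1 − 0.95⁹ = 37% for nine independent tests) belongs to this defect. It would apply to any nine subgroups. The third is that omitting infant sex is an error because the background reports a benefit in girls and says "however among the boys, it did not differ between groups". That study compared enteral feeds given to infants, and sex is already a covariate in the adjusted model. Adding it is a preference.

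**Conclusion.** The point holds in a limited form. Gestational age at delivery and capsule-count compliance are presented as a priori effect modifiers although both arise after randomisation; realised duration would be a third. The gestational-age bands as printed overlap.

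The consequence is uneven. For compliance it can be large: about 16% to 72% false-positive interactions, with a false dose-response gradient, if a prognostic factor drives compliance in the DHA arm only with r between 0.2 and 0.5. For gestational age it is small: within-band bias of a few hundredths of an SD in most assumed settings, reaching about 0.11 SD only if DHA lengthens gestation by a full week, with the interaction test near 5% throughout. It would therefore be wrong to conclude that the gestational-age interaction test is inflated, or that the primary DASII comparison is compromised. All sizes rest on the assumed correlations, not on trial data.

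**What to change.** In the Subgroup analyses section:
- Restrict the a priori list to variables known at enrolment.
- Replace gestational age at delivery and realised duration with gestational age at enrolment, as a continuous modifier or in disjoint bands. It is established at eligibility (Table 2) and sets the planned prenatal duration. If planned duration was meant all along, say so.
- Move compliance to a separately labelled exploratory analysis, for example a complier-average analysis that uses allocation as the instrument and the capsule counts being recorded. State its assumption that allocation affects DASII only through the capsules taken.
- If results by gestational age at delivery are still wanted, print non-overlapping bands and label them a non-randomised comparison.

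The cost is wording. No new data are needed, as all the items are being collected (the article reports about 70% delivered and 15% completed). The change can be made before the analysis team is unblinded, which the Blinding section sets at the last infant's first birthday.
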